**Sensitivity analyses for primary outcome**

#### *Missing data*

#### We will perform two sensitivity analyses to assess the robustness of our primary analysis to different assumptions regarding the missing data. These sensitivity analyses will be performed for the primary outcome (change in weight at 12 months).

#### A complete case analysis, where only patients with recorded data at 12 months are included

- An analysis which assumes data missing at 12 months is missing-not-at-random.

We will perform the second sensitivity analysis (where data missing at 12 months is assumed to be missing-not-at-random) using the formula ∆ = ∆_CC_ + Y_1_P_1_ – Y_2_P_2_, where ∆ is the treatment effect under the missing-not-at-random scenario, ∆_CC_ is the treatment effect from a complete case analysis, Y_1_ and Y_2_ are the assumed mean responses for participants with missing data in treatment groups 1 and 2 respectively, P_1_ and P_2_ are the proportion of participants who were excluded from the analysis in groups 1 and 2 respectively, and groups 1 and 2 represent the intervention and control groups respectively. The standard error for ∆ is assumed to be approximately equal to the standard error for ∆_CC._  Y_2_ will be varied between -10, -5, -2.5, 0, 2.5, 5, and 10. Negative values indicate the participant lost weight at 12 months, positive values indicate they gained weight, and a value of 0 indicates there was no change from baseline. For each value of Y_2_, Y_1_ will be set to Y_2_ - 5, Y_2_, and Y_2_ + 5.

For example, for Y_2_ = 10, this would indicate an assumption that patients in treatment arm 2 (the control arm) who were lost to follow-up at 12 months, had gained 10kg on average at 12 months. Y_1_ would vary between 5, 10, and 15, indicating the assumption that patients in treatment arm 1 (the intervention arm) who were lost to follow-up had gained 5kg on average at 12 months (5kg less than those in the control arm), 10kg (the same amount as those in the control arm), or 15kg (5kg more than those in the control arm).

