**Missing data for outcomes**

For outcomes that are measured at multiple time points during follow-up, we have based our analysis strategy on that proposed by White et al 2011[7]. To deal with incomplete data (i.e. when patients have missing data at one of the follow-up time points) we will:

1. Attempt to follow up all randomised patients even if they withdraw from the study
2. Perform a main analysis of all observed data that are valid under a plausible assumption about the missing data
3. Perform sensitivity analyses to explore the effect of departures from the assumptions made in the main analysis
4. Account for all randomised participants, at least in the sensitivity analyses

We will therefore (a) include all patients with at least one post-randomisation assessment (i.e. if they have recorded data for at least one follow-up time point) in the analysis; (b) use mixed-effects models adjusted for baseline covariates, which assumes that the data are missing-at-random (i.e. they are missing based on their observed outcome at other time-points, and other patient characteristics); and (c) perform sensitivity analyses under other missing data assumptions (e.g. that patients who were lost-to-follow-up gained more weight than patients who remained in the trial).

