**Analysis of primary outcome**

The primary outcome (change in weight at 12 months post-randomisation) will be analysed using a mixed-effects linear regression model. The model will include change in weight at 1, 2, 6 and 12 months as outcomes.

The model will include a random intercept for ‘cluster’ (group or nurse, depending on treatment arm). The correlation between observations at different time points from the same patient (1, 2, 6, and 12 months) will be modelled using an unstructured correlation structure. The model will be estimated using restricted maximum likelihood (REML). Treatment arm, time point (month 1, 2, 6, or 12), and the interaction between treatment arm and time point will be included in the model as fixed factors. Time point will be included as an indicator variable. The covariates listed in section 5 will also be included in the model as fixed factors.

The analysis will be implemented in Stata as follows:

mixed outcome treatment##time covariates || cluster_id:, || ///

patient_id:, noconstant residuals(unstructured, t(time)) stddev reml dfmethod(kroger)

If this model fails to converge, we will run the model again using the correlation structure

*residuals(ar 2 , t(time))*. If the model still fails to converge, we will use *residuals(ar 1 , t(time))*.

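### The missing-not-at-random grid is anchored on the complete-case effect, not the primary estimate, and its formula does not fit the stated meaning of Y1 and Y2

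*SAP*

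**What the plan says.** **Primary analysis.** Under *Analysis of primary outcome*, 12-month weight change is estimated from a mixed model: "The model will include change in weight at 1, 2, 6 and 12 months as outcomes". Under *Missing data for outcomes*, the assumption is that data are missing at random: "they are missing based on their observed outcome at other time-points, and other patient characteristics".

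**Purpose of the sensitivity analyses.** The same section undertakes to "Perform sensitivity analyses to explore the effect of departures from the assumptions made in the main analysis". *Sensitivity analyses for primary outcome* says that they are to "assess the robustness of our primary analysis to different assumptions regarding the missing data".

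**What is planned.** Two analyses are listed. One is a complete-case analysis. The other is Δ = Δ_CC + Y1P1 − Y2P2. Its starting value, Δ_CC, "is the treatment effect from a complete case analysis". Of the two Y terms, the SAP says that they "are the assumed mean responses for participants with missing data in treatment groups 1 and 2 respectively". On their scale, it explains that "a value of 0 indicates there was no change from baseline". Of the two P terms, it says that they "are the proportion of participants who were excluded from the analysis in groups 1 and 2 respectively". Y2 takes seven values from −10 to +10, and Y1 is set to Y2 − 5, Y2 or Y2 + 5, which makes 21 scenarios. The worked example reads Y2 = 10 as a mean gain of 10 kg. The standard error is taken to be that of Δ_CC.

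**The concern.** Two features of the formula do not fit the rest of the plan.

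- **Anchor.** The complete-case effect uses none of the 1, 2 and 6 month weights of participants who lack a 12-month weight. The primary model uses them. A grid built on Δ_CC therefore does not start from the assumption whose robustness is in question, and no planned setting stands for that assumption.
- **Meaning of Y.** Adding Y1P1 − Y2P2 to the completers' difference is correct algebra only if each Y is the mean in the missing minus the mean in the observed. The SAP defines and illustrates Y as an absolute change from baseline.

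At stake is how the sensitivity table is read. Its rows would carry labels, such as no change among the missing, that the computed values do not represent, and its centre would be a result other than the primary one.

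**Working it through.** **Inputs from the SAP** (*Sample size determination*): loss of 3 kg (WAP) and 0.4 kg (usual care) among those followed up, 50% missing in each arm, SD 3. Losses are negative in the formula, so the observed means are m1 = −3 and m2 = −0.4.

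**Step 1. The SAP's own dilution.** If the missing have no change:
- WAP: 0.5 × 3 + 0.5 × 0 = 1.5 kg
- usual care: 0.5 × 0.4 + 0.5 × 0 = 0.2 kg
- difference: 1.3 kg, as stated in the SAP.

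**Step 2. The same scenario in the sensitivity formula.** With Y1 = Y2 = 0 and P1 = P2 = 0.5, Δ = −2.6 + 0 − 0 = −2.6 kg. The effect is not diluted at all.

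**Step 3. The formula that absolute means require.** Δ = (1 − P1)m1 + P1Y1 − (1 − P2)m2 − P2Y2. At zero this gives 0.5 × (−3) − 0.5 × (−0.4) = −1.3 kg, which agrees with Step 1. The SAP formula differs from it by P1m1 − P2m2 = −1.5 + 0.2 = −1.3 kg in every scenario, in favour of WAP. At these inputs the SAP grid runs from −5.1 to −0.1 kg, and the weighted-mean version from −3.8 to +1.2 kg.

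**Step 4. What the 21 scenarios contain.** With P1 = P2 = P, the shift is (Y1 − Y2)P, and Y1 − Y2 is only −5, 0 or +5.
- P = 0.5: −2.5, 0, +2.5 kg
- P = 0.3: −1.5, 0, +1.5 kg

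There are three distinct results, and seven of the 21 scenarios repeat the complete-case analysis. With unequal missingness there are more (at 0.5/0.4, shifts from −3.5 to +3.5 kg). Under equal missingness Δ_CC is the centre line of the grid.

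**Step 5. How far apart the two anchors can be.** This was simulated with 220/110 participants, SD 3 and about 50% missing, with dropout driven by 6-month weight change. A likelihood estimate using the 6-month value stood in for the mixed model. The correlation between 6 and 12 months and the dropout slopes (log-odds per kg) are assumptions; the SAP gives neither.

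| Dropout slope, one arm / other arm | Correlation | Gap between anchors |
|---|---|---|
| same in both arms | 0.5–0.7 | no bias; 0.14–0.20 kg by chance (mean absolute) |
| 0.3 / 0.15 | 0.5–0.7 | 0.25–0.35 kg |
| 0.3–0.5 / 0 | 0.5 | 0.58–0.80 kg |
| 0.3–0.5 / 0 | 0.7 | 0.79–1.12 kg |

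In the one-arm cases the estimate that uses the earlier visit was unbiased and the complete-case estimate was not. Against the planned 1.3 kg, 0.6 to 1.1 kg is 46% to 85%.

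**The case against.** The strongest reply is that a completer-based analysis is a legitimate pattern-mixture method, and that its natural anchor is the complete-case estimate. If Y is read as missing minus observed, the formula is an identity under any dropout mechanism. For example, take a true effect of −1.30 kg, about 52% missing, correlation 0.7 and slopes 0.3/0. The complete-case effect is then −2.14, the missing-minus-observed mean is +1.61 in the WAP arm and about 0 in the control arm, and −2.14 + 0.52 × 1.61 = −1.30. Missing at random simply lies at a non-zero Y. The SAP's own example of a departure compares those lost with those who stayed, which suits this reading. Complete case is also reported separately, so a reader can separate the effect of dropping the early visits from the effect of the offset.

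All of this stands, and it rules out some stronger readings. A reader might infer that the analysis cannot test the missing-at-random assumption. That does not follow, because some value of the missing-minus-observed difference reproduces the primary estimate. A reader might infer that the primary result lies outside the scenarios. In every case simulated, the range of the grid bracketed it. A reader might also infer that a large error enters every scenario through the anchor. That requires dropout to depend on earlier weight in one arm only, which the SAP does not state; its sample-size section plans equal follow-up in both arms.

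The reply does not rescue the text as written. It needs Y to be a difference, and the SAP defines Y as an absolute change. Under that definition the formula contradicts the sample-size section (Steps 1 and 2).

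**Conclusion.** The concern holds on two counts, and the plan should be changed.

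- **Certain from the text.** The formula starts from Δ_CC, no scenario is defined to return the mixed-model result, and the grid is not laid out as departures from the primary assumption. The definition of Y and the formula are incompatible: 2.6 kg against 1.3 kg at 50% missing with no change among the missing.
- **Dependent on assumptions.** The gap between the anchors is near zero on average if dropout works alike in both arms, about 0.2 kg by chance. It is roughly 0.6 to 1.1 kg under one-arm dependence with the slopes and correlations in Step 5. Different mechanisms are plausible, because *Timing of data collection* gives the WAP arm monthly sessions in months 3 to 12 and the control arm only the 6 and 12 month visits. The SAP does not show that they occur.

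The primary analysis itself is unaffected.

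**What to change.** Replace the formula by Δ = Δ_primary + d1P1 − d2P2, where:
- Δ_primary is the 12-month effect from the primary mixed model;
- P1 and P2 are the proportions of randomised participants without a 12-month weight;
- d1 and d2 are the assumed mean departures of the unobserved 12-month changes from their missing-at-random prediction.

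Setting d1 = d2 = 0 then returns the primary result. Take the standard error from the primary model in place of the complete-case one. Restate the grid and the worked example as departures, with d1 and d2 varied separately so that the scenarios do not collapse to three. Keep the complete-case analysis as the separate analysis already listed.

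If absolute assumed means are preferred, use (1 − P1)m1 + P1Y1 − (1 − P2)m2 − P2Y2, with m1 and m2 the observed 12-month means, and add d1 = d2 = 0 around the primary estimate as the reference scenario. The complete-case standard error does not carry over to this version, because the observed means are weighted by 1 − P; it must be derived anew.

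The cost is SAP wording and simple arithmetic, with no new data and no new model. The drawback is that the present values, chosen as absolute kilogram changes, need a fresh justification as departures.

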**Sample size determination**

A clinically significant effect can be achieved with 3-5 kg weight loss in obese people.[3] We assumed that WAP would increase weight loss by 2.6kg compared with usual care (WAP 3kg vs. usual care 0.4kg) for participants available for follow-up at one year, and that there would be no difference in weight loss between treatment groups for participants not available for follow-up. Assuming that 50% of participants in both treatment groups were available for follow-up at one year, the difference in weight loss between groups would be 1.3kg (WAP 1.5kg vs. usual care 0.2kg). Assuming a standard deviation of 3 in both treatment groups, and a 5% two-sided significance level, we would require 112 participants in each group to detect this mean difference with 90% power. Our estimate of 50% loss to follow-up is conservative and based on international experience in this field and existing data from similar underprivileged and highly mobile populations and interventions.

To account for potential clustering effects due to group treatment in the intervention arm, assuming a mean cluster size of 18 and an intra-cluster correlation coefficient of 0.05, a total of 208 individuals will be required in the intervention arm. The same power can be achieved with 108 in the control arm and 216 in the intervention arm which we have increased to 110 in the control arm and 220 in the intervention arm to give an allocation ratio between the two arms (2:1) which can be expressed in whole numbers. Thus we require a total of 330 individuals for the entire study

1. **DATA COLLECTION**

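### The missing-not-at-random formula needs missing-minus-observed differences within arm, but the SAP defines its inputs as absolute changes from baseline

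*SAP*

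**What the plan says.** The SAP section on sensitivity analyses for the primary outcome plans two missing-data analyses: a complete-case analysis and one that lets data missing at 12 months be missing not at random. The second is done "using the formula ∆ = ∆_CC_ + Y_1_P_1_ – Y_2_P_2". Group 1 is WAP and group 2 is control. The inputs are defined as follows:

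- "Y_1_ and Y_2_ are the assumed mean responses for participants with missing data in treatment groups 1 and 2 respectively".
- The two P terms give the share of each arm left out of the complete-case analysis.
- On the scale of Y, negative values are weight lost, positive values are weight gained, and "a value of 0 indicates there was no change from baseline".
- In the worked example, Y2 = 10 means that control patients "who were lost to follow-up at 12 months, had gained 10kg on average at 12 months".

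Y2 takes seven values from –10 to 10. "For each value of Y_2_, Y_1_ will be set to Y_2_ - 5, Y_2_, and Y_2_ + 5", which makes 21 scenarios. The standard error is taken as approximately that of the complete-case effect.

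Two other sections bear on this. Under missing data for outcomes, the SAP gives as an example of a departure to explore "that patients who were lost-to-follow-up gained more weight than patients who remained in the trial". In the sample size section, with half of each arm lost and no difference between arms among those lost, "the difference in weight loss between groups would be 1.3kg (WAP 1.5kg vs. usual care 0.2kg".

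**The concern.** The definition, the meaning of zero and the worked example all put Y on the scale of absolute change from baseline. The formula leaves the observed effect at full weight and adds the missing participants' mean on top, so the weights in each arm sum to 1 + P instead of 1. The formula and the text therefore describe different analyses.

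This matters because the SAP replaces the protocol's baseline-carried-forward rule with a mixed model that relies on missing at random, plans for 50% loss, and undertakes to account for all randomised participants at least in the sensitivity analyses. The complete-case analysis does not do that, so this formula has to. Readers will take the row labels literally. The row for dropouts at their baseline weight, which is the closest link to the protocol's rule, simply repeats the complete-case result.

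**Working it through.** **Inputs** (SAP, sample size section): completer mean changes M1 = –3 kg (WAP) and M2 = –0.4 kg (control), so Δ_CC = –2.6 kg; P1 = P2 = 0.5; SD 3. Negative Δ favours WAP.

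**The plan's own figure.** With those lost contributing zero: 0.5 × (–3) – 0.5 × (–0.4) = –1.5 + 0.2 = –1.3 kg. This reproduces the SAP's 1.3 kg and weights the observed means by 1 – P.

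**Correct formula for absolute Y.** The mean over all randomised in an arm is (1 – P)M + PY = M + P(Y – M). Hence

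Δ = Δ_CC + P1(Y1 – M1) – P2(Y2 – M2).

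The SAP's formula minus this is P1M1 – P2M2, which does not depend on Y1 or Y2.

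**Scenarios at planning values.** With equal P only Y1 – Y2 matters, so the 21 scenarios collapse to three results:

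| Scenario | SAP formula | Correct for absolute Y | Shift |
|---|---|---|---|
| Y1 = Y2 – 5 | –2.6 – 2.5 = –5.1 | –1.3 – 2.5 = –3.8 | –1.3 |
| Y1 = Y2 | –2.6 | –1.3 | –1.3 |
| Y1 = Y2 + 5 | –2.6 + 2.5 = –0.1 | –1.3 + 2.5 = +1.2 | –1.3 |

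The last row changes sign.

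**Two checks.**
1. Y1 = Y2 = 0: the SAP formula returns Δ_CC whatever P1 and P2 are. At the planning values that is –2.6 kg against –1.3 kg. A simulation of individual data gave –1.30.
2. Missing participants like the observed (Y1 = –3, Y2 = –0.4): Δ should equal Δ_CC = –2.6. The SAP formula gives –2.6 – 1.5 + 0.2 = –3.9.

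**How the shift P1M1 – P2M2 varies.** The last three rows use completer means that are assumed, not taken from the SAP; all loss rates other than 50%/50% are also assumed.

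| M1, M2 | Loss WAP / control | Shift (kg) |
|---|---|---|
| –3, –0.4 | 50% / 50% | –1.30 |
| –3, –0.4 | 30% / 30% | –0.78 |
| –3, –0.4 | 30% / 50% | –0.70 |
| –3, –0.4 | 50% / 30% | –1.38 |
| –3, –2 | 30% / 50% | +0.10 |
| –2, –2 | 50% / 50% | 0 |
| –2, –2 | 30% / 50% | +0.40 |

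**Standard error with absolute Y.** The arm estimate (1 – P)M + PY has variance of about (1 – P)²Var(M) + P(1 – P)(Y – M)²/N; the second term is the uncertainty in P. Assume 220/110 randomised, half observed, and a design effect of 1 + 17 × 0.05 = 1.85 in WAP only. Then the complete-case SE is 3√(1/55 + 1.85/110) = 0.56, with variance 0.315.

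- Y1 = Y2 = 0: 0.25 × 0.315 + 0.25 × 9/220 + 0.25 × 0.16/110 = 0.089, so SE ≈ 0.30.
- Y1 = Y2 = 10: 0.25 × 0.315 + 0.25 × 169/220 + 0.25 × 108.16/110 = 0.517, so SE ≈ 0.72.

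The SAP's 0.56 is too large in the first case and too small in the second.

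**The case against.** The strongest reply is that the formula is what was meant and only the wording is wrong. The SAP's stated aim under missing data for outcomes compares those lost with those who stayed, and both the formula and the standard-error rule fit that. On this reading the computed numbers are valid, but the row labelled as no change from baseline in fact describes dropouts who resemble the completers in their own arm. This stands as a reason to put the redefinition of Y first among the fixes. It does not remove the problem, because the definition, the meaning of zero and the example all say otherwise, and a reader of the results table would be misled.

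Three stronger readings are tempting, and the SAP does not support them.

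- *The error always favours WAP, so a fragile result would always look robust.* It does so only when P1M1 is below P2M2. That holds at the planning values, but the shift is zero or reversed in the last three rows of the table above.
- *The error equals the whole powered effect.* That is true at 50% loss, which the SAP itself calls conservative. At 30% loss in both arms the shift is 0.78 kg against an overall effect of 0.7 × 2.6 = 1.82 kg, about 43%.
- *The confidence intervals are simply about twice too wide at 50% loss.* That treats P as known. It is roughly right near the completer means and wrong at the ends of the grid, where the SAP's standard error is too small.

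**Conclusion.** The formula and the text around it conflict, and the SAP should be corrected before the scenario table is produced. Followed literally, all 21 scenarios carry the same error, P1M1 – P2M2. Under the SAP's planning means and 50% loss in both arms this is 1.3 kg towards WAP; at 30% loss it is 0.78 kg. The actual size and direction depend on the observed completer means and dropout in each arm, which the SAP cannot give. The conflict itself does not depend on those values.

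The reach is limited. The primary mixed model, the complete-case analysis, the secondary outcomes and the sample size are not affected. The weight of the point comes from this being the only planned analysis of departures from missing at random through loss to follow-up.

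**What to change.** Choose one of two routes.

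(a) Keep the formula. Redefine Y1 and Y2 as the mean 12-month change of missing participants minus that of observed participants in the same arm, and rewrite the sentence on the value of zero and the worked example to match. The approximate standard-error rule can stay if the SAP says that it treats P as fixed. This is the smaller change and fits the aim stated under missing data for outcomes.

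(b) Keep Y as absolute change from baseline. Replace the formula with Δ = Δ_CC + P1(Y1 – M1) – P2(Y2 – M2), where M1 and M2 are the adjusted completer means at 12 months. Replace the standard-error rule with a cluster bootstrap that resamples all randomised participants, not completers only, or with the square root of (1 – P)²Var(M) + P(1 – P)(Y – M)²/N summed over arms.

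Either route changes one formula or a few sentences and needs no new data. Route (b) adds a little analysis work and, at the planning values, gives a scenario table less favourable to WAP.

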**Overall study design and plan**

Target for randomisation: 220 intervention and 110 control participants

Date of first randomisation: 27/09/2012

Date of last randomisation: 30/01/2014

Trial design: Individually randomised, parallel group

Who is blinded: Researchers affiliated with the study team conducting measurements at 6 and 12-month follow-up. Patients and those delivering the intervention are aware of the patient’s treatment allocation.

Randomised Interventions: Intervention (WAP) vs. control (Nurse counselling)

Allocation ratio: 2:1

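### Every missing-not-at-random scenario is given the complete-case standard error, which is the wrong standard error over most of the planned grid; the size and direction of the error depend on what Y means

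*SAP*

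**What the plan says.** The SAP (Sensitivity analyses for primary outcome, Missing data) plans two analyses: complete cases, and a missing-not-at-random analysis. The second computes Δ = Δ_CC + Y₁P₁ − Y₂P₂, with 1 for the intervention and 2 for control. Y is described as the mean response assumed for those with missing data, and P as the share left out of the analysis in that arm. Y₂ "will be varied between -10, -5, -2.5, 0, 2.5, 5, and 10", and Y₁ is set to Y₂ − 5, Y₂ or Y₂ + 5. That makes 21 scenarios, with Y₁ reaching 15 kg in absolute value. In all of them the standard error of Δ "is assumed to be approximately equal to the standard error for" Δ_CC. No limit is given for this approximation.

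The planning values are in other sections:

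- Overall study design and plan: "Target for randomisation: 220 intervention and 110 control participants".
- Sample size determination: "Assuming that 50% of participants in both treatment groups were available for follow-up at one year" and "Assuming a standard deviation of 3 in both treatment groups", with a mean group size of 18 and an intra-cluster correlation of 0.05 in the intervention arm.

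**The concern.** P₁ and P₂ are results of the trial. Multiplying them by assumed changes of up to 10 kg (control) or 15 kg (intervention) adds variance that the complete-case standard error does not contain. The offsets are large next to an SD of 3 kg, and 50% dropout is where P(1−P) is greatest.

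The definition of Y raises a second difficulty. The formula treats Y as a shift relative to the observed mean, while the text and its worked example treat Y as the actual mean change of the missing participants. The two readings are different estimators with different standard errors, and the complete-case value is correct for neither across the grid.

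Of the two missing-data analyses, only this one departs from missing-at-random. Its purpose is to show which assumptions would overturn the conclusion. With wrong intervals, a scenario can be reported as excluding zero when it should not, or the reverse.

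**Working it through.** **Plan's own figure.** The SAP gives no numerical standard error for this analysis, so the sample size is reproduced to confirm the inputs. With "a 5% two-sided significance level", "the difference in weight loss between groups would be 1.3kg" and SD 3, n = 2(1.96 + 1.2816)² × 9 / 1.3² = 111.9, which agrees with "we would require 112 participants in each group to detect this mean difference with 90% power". Clustering gives 112 × (1 + 17 × 0.05) = 207.2, rounded up to the SAP's 208.

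**Inputs.** n₁ = 220, n₂ = 110, P₁ = P₂ = 0.5, SD = 3 kg. With half of each group of 18 observed, the intervention design effect is 1 + (9 − 1) × 0.05 = 1.4. Control clustering by nurse is ignored, because the SAP gives no planning value for it.

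**Complete-case standard error.** SE_CC² = 9 × 1.4/110 + 9/55 = 0.1145 + 0.1636 = 0.2782, so SE_CC = 0.527 kg.

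**Reading A: the formula as written (Y is a departure from the observed mean).** With binomial P, uncorrelated with Δ_CC:

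Var(Δ) = SE_CC² + Y₁²P₁(1−P₁)/n₁ + Y₂²P₂(1−P₂)/n₂.

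At (15,10) the added terms are 225 × 0.25/220 + 100 × 0.25/110 = 0.2557 + 0.2273 = 0.4830. The standard error is √(0.2782 + 0.4830) = 0.872, a ratio of 1.65 to the planned value. Coverage is 2Φ(1.96/1.654) − 1 = 76%.

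**Reading B: Y as the text defines it (absolute mean change of the missing).** The matching estimator in each arm is (1−P) × observed mean + P × Y, with variance

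(1−P)² Var(observed mean) + (Y − observed mean)² P(1−P)/n, summed over arms.

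The assumed observed means are −3 and −0.4 kg, from the Sample size determination section. At (15,10): 0.25 × 0.2782 + 18² × 0.25/220 + 10.4² × 0.25/110 = 0.0695 + 0.3682 + 0.2458 = 0.6836, so the standard error is 0.827.

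| (Y₁,Y₂) | Planned SE | SE, A | A / planned | Coverage, A | SE, B | B / planned |
|---|---|---|---|---|---|---|
| (0,0) | 0.527 | 0.527 | 1.00 | 95% | 0.283 | 0.54 |
| (−5,0) | 0.527 | 0.554 | 1.05 | 94% | 0.273 | 0.52 |
| (2.5,2.5) | 0.527 | 0.547 | 1.04 | 94% | 0.351 | 0.67 |
| (5,5) | 0.527 | 0.603 | 1.14 | 91% | 0.457 | 0.87 |
| (10,5) | 0.527 | 0.670 | 1.27 | 88% | 0.573 | 1.09 |
| (10,10) | 0.527 | 0.787 | 1.49 | 81% | 0.712 | 1.35 |
| (15,10) | 0.527 | 0.872 | 1.65 | 76% | 0.827 | 1.57 |

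Over all 21 pairs:

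- Under A, coverage is below 93% in 14 scenarios and below 90% in 8.
- Under B, the planned standard error is too large in 14 and too small in 7, with ratios from 0.52 to 1.57.

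**Simulation of A** (40,000 trials, no clustering). At (5,5) the empirical SD of Δ was 0.574 and at (15,10) it was 0.855, against a mean planned standard error of 0.497. Coverage was 91.1% and 74.8%.

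**Sensitivity of A to the inputs.**

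- At 30% missing (design effect 1.58) the largest ratio is 1.71, with 75% coverage.
- With an assumed completer SD of 6 kg, SE_CC² is 4 × 0.2782 = 1.113. The largest ratio is √((1.113 + 0.483)/1.113) = 1.20, with 90% coverage.

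**The two readings also differ in the estimate.** With the planning means and Y₁ = Y₂ = 0, the formula returns −3 − (−0.4) = −2.6 kg. Reading B returns 0.5 × (−3) − 0.5 × (−0.4) = −1.3 kg, which is the dilution that the SAP's own sample size uses.

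**The case against.** **P can be taken as fixed.** Given the realised dropout, Y₁P₁ and Y₂P₂ are constants and the complete-case standard error is exact for the formula. That is arithmetically right. But dropout is an outcome of the trial, and the SAP does not limit its inference to the realised proportions. For an effect in the randomised population, P is an estimate.

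**The SAP declares an approximation.** It does, and for small |Y| in the formula as written the approximation is good. It is not good at the edges of the SAP's own grid.

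**SD 3 may be too small for completers.** This stands as a limit on the size. The SAP applies SD 3 to the diluted comparison. If the missing half had exactly zero change, 9 = 0.5s² + 0.25 × mean² gives s = 3.7 (intervention, mean 3) and 4.2 (control, mean 0.4). Then SE_CC² = 13.5 × 1.4/110 + 17.92/55 = 0.498, and the ratio at (15,10) falls to √((0.498 + 0.483)/0.498) = 1.40.

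**It is only a sensitivity grid.** True. When Y₁ and Y₂ differ by 5 kg, the formula moves the estimate by 2.5 kg at P = 0.5, far more than the largest change in standard error, 0.872 − 0.527 = 0.345 kg. The scenarios with Y₁ = Y₂ have no such shift, and there the standard error matters more.

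**Stronger readings to avoid.** A reader might infer that the planned intervals are too narrow whichever way Y is read. Reading B contradicts this, since most of them would be too wide. A reader might also infer that the omitted variance generally exceeds the variance kept. Under A that holds in only 4 of 21 scenarios, those with (Y₁,Y₂) = ±(10,10) and ±(15,10), and in none with SD 6.

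**Conclusion.** The point holds in a limited form. The complete-case standard error is not the standard error of Δ over the planned grid.

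- **Formula as written:** it is correct at (0,0), nearly so when both |Y| are 2.5, and materially too small once both |Y| reach 5. The correct value is 14% larger at (5,5) and up to 65% larger at (15,10), with about 76% coverage there.
- **Y as the text defines it:** the error runs in both directions, and more often the planned value is too large (14 of 21) than too small (7 of 21).

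The figures rest on planning values for n, dropout and SD, a design effect of 1.4, independent dropout and, for the second reading, observed means of −3 and −0.4 kg. A larger completer SD shrinks the error under the formula as written; at 6 kg the worst case is 20%. The documents do not support a claim that the trial's false-positive rate is inflated, because the primary mixed-model test does not use this standard error. The change is worth making because the analysis exists to judge robustness and the correction is cheap.

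**What to change.** 1. Reconcile the formula with the definition of Y, stating whether Y is a departure from the observed mean or the absolute mean change of those missing.
2. Replace the standard-error sentence with the one that belongs to the chosen estimator:
   - **Departure from the observed mean:** keep Δ and use SE = √(SE_CC² + Y₁²P₁(1−P₁)/n₁ + Y₂²P₂(1−P₂)/n₂), with n₁ and n₂ the numbers randomised.
   - **Absolute mean change:** estimate each arm as (1−P) × observed mean + P × Y, with variance (1−P)² Var(observed mean) + (Y − observed mean)² P(1−P)/n, summed over arms.
3. Alternatively, bootstrap whole clusters within arm and recompute the observed means or Δ_CC, P₁, P₂ and Δ in each resample. This serves either definition and allows for dropout that clusters by group or nurse. It will be rough if clusters are few: 220/18 is about 12 intervention groups, and the SAP does not give the number of nurses.

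The two formulas must not be mixed. Putting Y minus the observed mean into the first expression, when Y is an absolute change, overstates the standard error by 14% to 95% across the grid (SD 3, design effect 1.4).

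The cost is a sentence or two in the SAP and a little code, with no new data. Some sensitivity intervals will become wider, and under the absolute definition many will become narrower.
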